## Abstract

**Introduction:**

Smoking rates among individuals in treatment for opioid addiction are close to five times that of the general public. Moreover, drug-addicted smokers have a premature mortality rate four times greater than drug-addicted non-smokers. The aim of this pilot study was to investigate whether contingency management (CM) can be successfully added to evidence-based stop smoking treatment in individuals undergoing treatment for opioid addiction and assess preliminary evidence for its impact.

**Participants:**

Forty tobacco smokers currently undergoing treatment for opioid addiction.

**Intervention:**

Escalating with reset CM as an adjunct to standard smoking cessation treatment. Financial incentives will be administered over a 5-week period for either biochemically verified abstinence from smoking or attendance at the clinic. Participants will be randomised to conditions stratified on current levels of smoking (high or low).

**Objectives and analyses:**

To assess whether a CM intervention can be successfully added to standard stop smoking services treatment, in patients undergoing outpatient treatment for opioid addiction. This will be measured as the number of people completing the 5 weeks of the intervention.

**Ethics and dissemination:**

Ethics approval for the study was granted on the 16 June 2016 by the London—city and east (reference 16/LO/0990) ethics committee. The pilot study was retrospectively registered on clincaltrials.gov in January 2017 (ID: NCT03015597). A SPIRIT checklist and figure are available for this protocol. It is planned that the results of this study will be published in an academic journal.

Strengths and limitations of this studyExtends an extensively tested evidence-based intervention to a novel treatment population.Implements a randomised controlled experimental design.Due to constraints of the intervention, blinding of both participants and treatment centre staff is not possible.

## Background

Tobacco smoking is the leading cause of premature death in the Western world,^1^ currently killing six million people per year across the globe, predicted to rise to eight million people annually by 2030.^2^ In England alone, smoking killed 74 000 people in 2014.^3^ Consequently, tobacco smoking places a large economic burden on both the National Health Service and the larger UK economy. It has been estimated that tobacco smoking costs the NHS approximately two billion pounds per year, with a total cost to the UK economy of approximately 13 billion pounds annually.^4^

In 2016, smoking prevalence in the general UK population fell below 17% for the first time.^5^ However, despite this encouraging downwards trend, smoking prevalence among those in treatment for drug addiction remains high, with a prevalence of 88% recorded in the UK in 2013^6^ and little change observed in the 20 years from 1988 to 2008.^7^ Drug-addicted smokers also have a fourfold greater premature mortality rate than non-smokers.^8^ This situation is further exacerbated by evidence showing that the efficacy of the standard stop smoking treatment currently used is nearly halved when an individual has used illicit drugs in the past 30 days.^9^ There is, therefore, a great need for the development of novel interventions for tobacco smoking for those in drug addiction treatment that can bolster the efficacy of current interventions. One of the highest rates of smoking prevalence in substance abuse treatment is observed in opioid addictions treatment, ranging between 84% and 98%.^7 10–13^ Moreover, those in treatment for opioid addiction report high rates of interest in stop smoking treatment,^10 11^ making them an ideal population for the development of interventions for tobacco smoking in substance abuse treatment.

Contingency management (CM) is a behavioural intervention based on the principles of operant conditioning, whereby changes in behaviour are brought about by positively rewarding desired behaviours. CM has been shown to be an effective intervention for drug use during opioid addiction^14^ and has been recommended for use in opioid addictions in the UK for some time.^15^ Some studies show promising results for CM in smoking cessation during treatment for opioid addiction^16–20^; however, this remains under-researched. Moreover, none of the currently published studies investigating this were carried out in the UK, or alongside standard stop smoking treatment.

The aim of the proposed pilot study was to assess whether a CM intervention can be successfully added to standard stop smoking services treatment in patients undergoing outpatient treatment for opioid addiction.

## Ethics

### Risks to participants

There is no known risk associated with the CM behavioural intervention. Smoking cessation can precipitate a number of uncomfortable withdrawal symptoms. These will be attenuated by the stop smoking services treatment provided at the treatment centre, an evidence-based treatment that includes nicotine replacement therapy (NRT), e-cigarettes and behavioural support. Any information recorded from participants will be anonymised using a participant ID number, the master sheet for which will be stored in a locked cabinet at the treatment centre. This ensures that no identifiable information will ever leave the treatment centre.

### Vouchers rather than cash

The treatment centre where the pilot study is being carried out did not want participants to be paid in cash so as not be able to buy cigarettes, alcohol or drugs. The ‘Love2Shop’ vouchers used as an alternative can be spent in a number of high street stores. Although cash vouchers have been shown to be more effective than vouchers in some case,^21^ other research has shown cash and monetary vouchers to be of equal efficacy.^22 23^ The use of monetary vouchers, therefore, should not negatively impinge on the efficacy of the current intervention. Participants will receive both the study intervention and standard stop smoking services treatment at no cost.

## Methods/design

This protocol was designed in accordance with the SPIRIT (Standard Protocol Items: Recommendations for Interventional Trials) statement. See online supplementary material for SPIRIT checklist and online supplementary figure.

10.1136/bmjopen-2017-017467.supp1Supplementary file 1

10.1136/bmjopen-2017-017467.supp2Supplementary file 2

### Objectives

Primary objective: To investigate whether a CM intervention can be successfully added to standard stop smoking services treatment, in patients undergoing outpatient treatment for opioid addiction, in order to identify any elements that need changing before carrying out a full-scale randomised controlled trial (RCT).

Secondary objective: To gather preliminary findings regarding the effects of the CM intervention on smoking in this group, and any possible effects the intervention may have on opioid addiction treatment outcomes.

### Participants, recruitment, inclusion criteria and randomisation

As this is a pilot study, the primary outcome is not the efficacy of the study intervention. Consequently, the sample size has not been calculated to ascertain efficacy. Instead, the method outlined by Viechtbauer *et al*
24 for calculating the sample size based on the probability of any issues that may arise has been used. A sample size of 40 using the above rationale is powerful enough to provide over 90% certainty of detecting any issues that occur with a probability of over 5%.

The study therefore aims to recruit 40 patients, all undergoing current treatment for opioid addiction and who smoke ten or more cigarettes a day. Participants will be recruited from the study site, an outpatient drug addiction treatment centre, either through self-referrals in response to advertisements shown in the treatment centre or referrals from treatment centre staff. Participants are eligible for inclusion if they want to quit smoking (complete abstinence), are aged between 18 and 65 years, undergoing pharmacological treatment for opioid addiction, smoke a minimum of 10 cigarettes per day and provide informed consent. Use of smoking cessation medication is not a criterion for exclusion. Participants will be ineligible for inclusion in the study if they exhibit insufficient English skills to understand study protocols, are currently undergoing treatment for other drugs of abuse or if taking part in other research. Pregnant women will not be excluded.

Participants will be randomised into either experimental (CM for abstinence) or control (CM for attendance) conditions when recruited into the trial. Randomisation will be performed by the principal investigator (PI), using the service provided by the company ‘sealed envelope’,^25^ and will be performed using random permuted blocks within strata. Randomisation will be stratified based on participants’ current smoking frequency (between 10 and 20 per day, and more than 20 per day^6^). All participants will be given at least 24 hours after being given an information sheet to decide whether to take part, and will provide written consent, collected by the PI ([name]).

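### Forty participants give about 87%, not over 90%, certainty of seeing at least once a problem that occurs with 5% probability

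*Protocol article*

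**What the plan says.** The sample-size paragraph of the protocol article is in the section Participants, recruitment, inclusion criteria and randomisation. It first sets efficacy aside: "the sample size has not been calculated to ascertain efficacy". In its place, a published method for "calculating the sample size based on the probability of any issues that may arise has been used". The result is then stated: 40 participants "is powerful enough to provide over 90% certainty of detecting any issues that occur with a probability of over 5" per cent. The recruitment target follows directly: "The study therefore aims to recruit 40 patients".

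The article prints no formula. It gives three inputs: the number of participants (40), the certainty (over 90%) and the threshold probability of a problem (5%). The statement concerns the whole sample. Nothing is said about the certainty within one arm, and no allocation ratio is given.

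Under Objectives, the primary objective is to find out what would have to be changed before a full-scale trial. Detecting problems is therefore the purpose that the sample size is meant to serve.

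**The concern.** The three stated figures do not fit together. Once two of them are fixed, the third follows from a one-line calculation, and 40 participants with a 5% threshold give less than 90%.

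Because the article disclaims an efficacy calculation, this sentence is the only numerical justification for recruiting 40. It also describes how well the pilot performs its main task. A planner of the full trial who relied on it would take the chance of missing a 5% problem altogether to be below 10%, when it is about 13%. That makes a finding of no problems look somewhat stronger than it is.

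**Working it through.** **Inputs**, all from the sample-size paragraph: n = 40; threshold p = 0.05; stated certainty over 90%.

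**Formula.** If each participant independently has probability p of showing the problem, the chance of seeing it at least once among n participants is 1 − (1 − p)^n. This is the natural reading of a rationale built on the probability of issues arising.

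**Step 1: the plan's own figure.**
1 − 0.95^40 = 1 − 0.1285 = 0.8715, or 87.1%. The stated figure of over 90% is not reproduced. The shortfall is 90 − 87.1 = 2.9 percentage points, and the chance of missing the problem is 12.9%.

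**Step 2: the sample size that the claim would need.**
n = ln(0.10) / ln(0.95) = 44.89, rounded up to 45. Check: 1 − 0.95^45 = 0.9006. The gap is 45 − 40 = 5 participants.

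**Step 3: the threshold that 40 participants support.**
p = 1 − 0.10^(1/40) = 0.0559. With 40 participants, 90% certainty holds for problems of about 5.6% or more.

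**Step 4: does another reading rescue the figure?**

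| Reading | Certainty with n = 40 |
|---|---|
| Poisson approximation, 1 − exp(−40 × 0.05) | 86.5% |
| Problem must be seen at least twice, p = 5% | 60.1% |
| Strictly above 5%: p = 5.1% | 87.7% |
| p = 5.5% | 89.6% |
| p = 5.6% | 90.03% |
| p = 6% | 91.6% |

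The sentence covers any problem above 5%, so it has to hold just above 5%. It fails from there up to about 5.6%. Rounding does not explain the difference either, since 87.1% does not round to more than 90%. Of the usual targets at p = 5%, 40 participants are enough for 85% (37 needed) but not for 90% (45 needed) or 95% (59 needed).

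**Step 5: scope, under an added assumption.** Some problems could arise only from making rewards depend on abstinence, and these can appear only in the experimental arm. If allocation is 1:1, which the article does not state, that arm has 20 participants. Then 1 − 0.95^20 = 0.6415, or about 64% at 5%. The 90% level is reached at p = 1 − 0.10^(1/20) = 0.1087, or about 10.9%. The article makes no claim to compare with these figures.

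**The case against.** **The formula is inferred.** The article cites the method without printing it, and the source was not available. This caveat stands. It does little to protect the figure, because the paragraph itself describes a probability-based detection argument and the variants tried in the working also fail to give over 90% at 5%.

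**The shortfall is small and nothing depends on it.** This also stands. The gap is 2.9 points, or a threshold of 5.6% in place of 5%, and for a 6% problem 40 participants already give 91.6%. Under Outcome measures, success is defined as completion by 60% or more of participants; under Planned analysis, the primary objective is reported descriptively. Neither uses the 90% figure, and no planned analysis interprets an absence of problems at that level. This limits the severity but does not make the sentence correct.

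**Stronger readings that the document does not support.** A reader might infer that the certainty is really only 64%, because abstinence-contingent rewards are given in one arm, and might set a 36% risk of missing a problem against the claimed 10%. The article makes no per-arm claim, so that comparison is not with anything it states. The 64% also rests on an unstated 1:1 allocation. Moreover, most feasibility problems can show up in all 40 participants: under CM intervention, both arms have the same reward values, escalation and reset, vouchers, CO readings and delivery of rewards, and recruitment, consent and the 6-month follow-up are common to both. Only problems tied to making the reward depend on abstinence are confined to one arm.

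A reader might also infer that the pilot is too small and must recruit 45. That follows only if 90% at exactly 5% is treated as a requirement. The article offers it as a rationale, and 87% does not make the pilot unfit for its purpose.

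**Conclusion.** The stated certainty is wrong on the article's own inputs. Under the at-least-once formula, 40 participants give 87.1% at a 5% problem probability and reach 90% only from about 5.6%; over 90% at 5% would need 45. The conclusion assumes that detection means at least one occurrence and that participants are independent, and it was reached without sight of the cited method paper.

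Severity is minor to moderate. The figure should be corrected because it is the sole numerical basis for the sample size in a pilot designed to find problems. The design, conduct, success criterion and analyses are unaffected. The one-arm figures mark a limit on what the statement covers and are not a second error.

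**What to change.** Keep the sample size at 40 and restate one sentence along these lines:

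> Forty participants give about 87% certainty of observing at least once a problem with 5% probability (90% for problems of about 5.6% or more).

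Optionally, add a note on scope: for problems arising only from abstinence-contingent rewards, and assuming 1:1 allocation with 20 participants per arm, the certainty is about 64% at 5%, and reaches 90% for problems of about 10.9% or more.

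The cost is one sentence of text, or two with the note. The stated figure becomes slightly less favourable. No further participants are needed and no procedure changes.

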### Study design

A two-arm randomised controlled pilot study with 6-month follow-up. The intervention will be provided as an adjunct to the standard smoking cessation treatment provided at the treatment centre, with CM rewards available during 2–5 weeks of the smoking cessation treatment. The study will be conducted in compliance with the principles of the Declaration of Helsinki,^26^ the principles of Good Clinical Practice and all applicable regulatory requirements.

### Opioid treatment

As part of the standard opioid treatment programme, the clinic offers both behavioural and pharmacological treatments. Pharmacological treatments include methadone, buprenorphine and in some cases a combination of buprenorphine and naloxone; each of these progresses from a daily supervised dose, to a daily unsupervised pickup to a weekly unsupervised pickup. All medication prescriptions are reviewed every 6 months. Clients are also allocated a key worker with whom they meet in person every 2 weeks to discuss their treatment, and who can refer them to a number of different behavioural support programmes. These include psychological therapies or group therapy for their drug use, or a number of other services for issues related to their drug use such as needle exchanges, bloodborne virus testing and domestic violence support. In the past, the clinic has implemented CM interventions as part of other research projects; however, CM has never been implemented as part of the standard opioid treatment programme.

### Standard treatment

Prior to the initiation of this study, the smoking clinic had not operated for several months; smoking cessation training was therefore readministered to clinic staff and the smoking cessation treatment relaunched prior to the start of the trial. The treatment runs at the same time each week, on a Monday afternoon between 2 and 4 PM. The standard smoking cessation treatment provided at the treatment centre follows the treatment programme set out by the National Centre for Smoking Cessation and Training (NCSCT)^27^ and The National Institute for Health and Care Excellence (NICE) guidelines for smoking cessation.^28^ This treatment combines manualised behavioural support to stop smoking with NRT and takes place over 6 weeks with one session per week. In the context of drug addiction treatment, service users are sometimes offered treatment over a slightly longer period of time. In the first meeting, the service user’s readiness and ability to quit is assessed, information for the remainder of the treatment programme is given and a quit date for the next week is set. For the remaining 5 weeks, clients attend the clinic to receive behavioural support and have their abstinence biochemically verified. In the study clinic, NRT is available free of charge to all individuals engaged with smoking cessation treatment, in the form of nicotine patches, gum, inhalators, mouth or oral spray and oral strips. At the time of the study, the clinic is also additionally offering (on a trial basis) e-cigarettes, which have a nicotine content of 18 mg/ml. These e-cigarettes are disposable and securely sealed, initially designed for use in high-security environments such as prisons.^29^ The smoking cessation treatment provided at the treatment centre does not include treatment with bupropion.

During the 6 weeks of treatment, service users are given a week’s supply of NRT or e-cigarettes at a time. At the end of the 6 weeks, service users are given a further 2-week supply of NRT or e-cigarettes before exiting the treatment. The type of NRT received is decided by clients with guidance from the cessation worker, and can constitute a single form of NRT or a combination of different types. Clients’ breath carbon monoxide (CO) levels are measured using a Bedfont piCO+ Smokerlyzer breath CO monitor. Measurements are taken at the initial visit and at each subsequent visit over the next 5 weeks, to biochemically verify self-reported abstinence from smoking (CO<10 ppm^30^). NRT and e-cigarette use is recorded throughout treatment. Participants are made aware of these procedures in the participant information sheet that they are given prior to signing consent to the study (see online supplementary appendix 1).

10.1136/bmjopen-2017-017467.supp3Supplementary file 3

### CM intervention

The CM intervention will run as an adjunct to the normal smoking cessation treatment, and follows an escalating with reset schedule. In escalating with reset CM, rewards increase in a set increment value for each successive verified display of the desired behaviour. When the desired behaviour is not observed, no reward is given, and the reward value for the next verified display of the desired behaviour is reset to that of the initial reward. Reward values then begin to rise again in the same way as before. The CM intervention will run for 5 weeks in total, starting in week 2 of the standard stop smoking services treatment and ending in week 6 (table 1). Randomisation will be performed after collection of demographics following taking of consent. Participants will be rewarded for smoking abstinence in the experimental condition, or for attending the smoking cessation clinic in the control condition. Smoking abstinence will be defined as a breath CO reading of <10 ppm, and attendance will be defined as attending the smoking cessation treatment at the clinic that week. After each smoking cessation treatment session, the cessation worker will fill out a slip that records each participant’s individual participant number and his or her breath CO for that day. The cessation worker will give these slips to the PI who will sit in an adjacent room and administer rewards where appropriate. All participant data will be recorded using participant numbers ensuring that no identifiable data leave the clinic, and will be stored in an encrypted file, separate to a sheet matching participant names to IDs which will be kept in a locked office at the treatment centre. Due to the nature of the CM intervention, it is not possible to blind participants to treatment allocation. Cessation workers will not be made aware of treatment allocation; however, they cannot be considered to be blinded to treatment allocation as it is possible that clients may discuss this with them.

**Table 1 T1:** Reward schedule

Smoking cessation treatment week No	1	2	3	4	5	6
CM week No		1	2	3	4	5
Reward value	£0.00	£5.00	£10.00	£20.00	£40.00	£40.00

Reward schedule for a participant that remains abstinent and/or attends all smoking cessation treatment meetings (dependent on condition) for the duration of the intervention. Maximum total reward: £115.

CM, contingency management.

Reward values will be the same in both conditions and begin at £5, doubling each time the incentivised behaviour is recorded to a maximum of £40. All rewards will be given as ‘Love2Shop’ vouchers. Over the course of the whole intervention, participants will be able to earn a maximum of £115 (table 1). At the end of the CM intervention, participants will be asked to complete a client satisfaction and well-being survey, which was previously used to assess client satisfaction of stop smoking services treatment.^31^

### Measures

#### Outcome measures

The primary outcome will be assessed by recording the number of participants completing the 5 weeks of the intervention in each condition. Success will be defined as 60% or more of participants completing treatment.

The secondary objectives of the study are to gather preliminary findings regarding the effects of the CM intervention on smoking in this group, and any possible effects the intervention may have on opioid addiction treatment outcomes. Smoking abstinence will be recorded as point prevalence and biochemically verified with abstinence defined as a breath CO reading of under 10 ppm^30^.Participants were informed that smoking cannabis would increase CO levels.

Participant medical records will be accessed after completion of the intervention to ascertain participants’ opioid addiction treatment, including treatment adherence, drug types (methadone, Subutex, so on), dosage and schedule (daily supervised pickup, weekly pickup, so on) as well as illicit drug use throughout the period of the trial.

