#### Follow-up measures

At the 6-month follow-up (see below for follow-up procedures), the following measures will be recorded:

Point prevalence smoking abstinence: Self-reported smoking abstinence for 7-days before follow-up and exhaled air CO<10 ppm.^30^

Continuous abstinence: Self-reported smoking abstinence since end of treatment and exhaled air CO<10 ppm. Participants smoking five or fewer cigarettes during the 6-month follow-up will be considered self-reported quitters.^30^

Illicit drug use, collected at the end of the study from participants’ medical records.

All those lost to follow-up will be treated as smoking.^30^

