#### Other measures

At the first stop smoking treatment session, a number of demographic and smoking behaviour variables will be recorded. The collection form for this information is shown in online supplementary appendix 2. As many contact details as possible will also be taken for the participants in order to increase the probability of participants being able to be followed-up. This will include the details of relevant friends and family members. Participants will also complete a satisfaction questionnaire on the last day of their participation in the trial, which will assess a number of satisfaction criteria including the value of incentives received (see online supplementary appendix 3).

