### Planned analysis

As the primary objective of the intervention does not entail any hypothesis testing, the only statistics reported for this will be descriptive, namely means and SD for the number of participants retained at the end of treatment in each condition. Baseline demographics will be compared between conditions using t-tests for continuous and χ^2^ test for categorical data to ensure that any differences in these are not driving any potential differences in retention.

For the secondary objectives, differences between the groups in smoking cessation will be investigated using χ^2^ test, differences between conditions on opioid use and opioid treatment during the intervention will be compared using t-tests and χ^2^ tests dependent on data and any questionnaire data will be reported using descriptive statistics. All statistics will be performed as two-tailed tests using an alpha value of 0.05.

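### No pre-randomisation window is stated for illicit or opioid use, so the unadjusted comparison of about 20 per arm loses precision and a chance difference at entry cannot be examined

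*Protocol article*

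**What the plan says.** Half of the secondary objective (Objectives) concerns possible effects of the intervention on opioid addiction treatment outcomes. The data come from records read afterwards (Outcome measures): "Participant medical records will be accessed after completion of the intervention to ascertain participants’ opioid addiction treatment". The list covers adherence, drug type, dosage and schedule, "as well as illicit drug use throughout the period of the trial". The trial-period limit attaches clearly only to illicit use; the treatment items have no stated window. Follow-up measures adds "Illicit drug use, collected at the end of the study from participants’ medical records".

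At entry, Other measures says that "a number of demographic and smoking behaviour variables will be recorded" and that "The collection form for this information is shown in online supplementary appendix 2". That appendix is not among the documents at hand.

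The section on participants, recruitment, inclusion criteria and randomisation stratifies on cigarettes per day only. Planned analysis states that "differences between conditions on opioid use and opioid treatment during the intervention will be compared using t-tests" or chi-squared tests, depending on the data, and names no covariate. The only baseline comparison it plans is of demographics, with retention in mind.

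**The concern.** Drug use and opioid treatment are likely to carry over from before entry. The section on opioid treatment says prescriptions are reviewed every 6 months, while the incentives run for 5 weeks. Much of what the records show during the intervention may therefore reflect where each participant started. With about 20 per arm and no stratification on drug use, the arms can differ at entry by chance. If no entry value is extracted, a reader who sees a difference during the trial has no means of checking whether it was there at the start.

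The article itself treats recent drug use as relevant to stopping smoking. Background says that the efficacy of standard stop-smoking treatment "is nearly halved when an individual has used illicit drugs in the past 30 days". An entry value would therefore also help to describe the groups in the cessation comparison.

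At stake is how precise and how readable a preliminary secondary result is.

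**Working it through.** The plan gives no precision or power figure for this comparison. Its sample size of 40 rests on detecting feasibility problems, so there is no figure of its own to reproduce here.

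**Inputs.** From the article: 40 participants, two arms, two-sided alpha 0.05, unadjusted t-test or chi-squared test. Assumed: equal arms of 20; a normally distributed amount of use; a correlation r of 0.3 to 0.8 between the value before and the value during the trial; a true effect of 0 or 0.8 SD.

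**Step 1: how often the arms differ at entry by chance.** The standard error of the baseline difference, in SD units, is √(2/20) = 0.316. The probability of a difference of at least 0.5 SD is 2 × [1 − Φ(0.5/0.316)] = 2 × [1 − Φ(1.58)] = 0.114, about 11%. For a yes/no measure of entry use, the exact binomial probability of a difference of at least 20 percentage points (4 of 20) is 23% at a prevalence of 30% or 70% and 27% at 50%.

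**Step 2: what adjustment gains, and whether the unadjusted test is valid.** In large samples the ratio of adjusted to unadjusted standard error is √(1 − r²). With 20 per arm it is slightly larger, because the slope has to be estimated. Simulation of 40,000 trials per setting gave:

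| Assumed r | √(1 − r²) | Simulated SE ratio | Unadjusted rejection, no effect | ANCOVA rejection, no effect | Unadjusted rejection, no effect, entry imbalance ≥ 0.5 SD | Power at 0.8 SD, unadjusted | Power at 0.8 SD, ANCOVA |
|---|---|---|---|---|---|---|---|
| 0.3 | 0.95 | 0.97 | 5.1% | 5.0% | 8% | 69% | 72% |
| 0.5 | 0.87 | 0.88 | 5.0% | 5.1% | 13% | 69% | 80% |
| 0.7 | 0.71 | 0.72 | 5.1% | 4.8% | 22% | 70% | 93% |
| 0.8 | 0.60 | 0.61 | 5.1% | 5.2% | 28% | 70% | 98% |

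With no true effect, the mean unadjusted estimate was 0.001 SD.

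**Step 3: how the conditional and overall rates fit together.** At r = 0.7, 11.3% of trials had an imbalance of at least 0.5 SD and rejected in 21.9% of cases. That contributes 0.113 × 0.219 = 2.5 percentage points. The overall rate was 5.1%, so the other 88.7% of trials rejected in (5.1 − 2.5)/0.887 ≈ 3% of cases. The test holds 5% on average over randomisations, by rejecting too often in imbalanced trials and too seldom in the rest. Without an entry value, nobody can tell which kind of trial this one is.

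**The case against.** The strongest reply is that allocation is randomised. Entry differences arise only by chance and the test's error rate already allows for them. That stands: a reader might infer that the comparison is confounded, or that an entry difference would bias it, and the design does not support this. Nor should the ordinary sampling error of a yes/no comparison with 20 per arm be charged to the missing baseline. At an assumed 50% prevalence it is √(2 × 0.5 × 0.5/20) = 15.8 percentage points, or about ±31 points at 95%, and the chi-squared test already accounts for it.

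A reader might also infer that no entry value of drug use will be collected at all. The article does not show that. Appendix 2 is not at hand, the start of the trial period is not defined, and the treatment items carry no stated window. What can be said is that the text names no such value and that the stated analysis would not use one.

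It would be too much to say that the analysis is unadjusted because the baseline is missing. The cessation comparison is also a plain chi-squared test, although smoking level is recorded at entry and used for stratification.

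Finally, the article disclaims a sample size for efficacy and calls these findings preliminary. The correlations are assumed. With key-worker meetings every 2 weeks, a 30-day look-back spans only about two of them, so the entry value may be coarse and the correlation at the lower end of the range. All of this stands and limits the weight of the point. It does not remove the gain from a look-back in records that will be opened anyway.

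**Conclusion.** The point holds as one of precision and interpretability, not validity. The article states no pre-randomisation window for illicit or opioid use and plans an unadjusted comparison of values during the intervention. At an assumed correlation of 0.5 to 0.7, adjustment would cut the standard error by about 12% to 28%. The same range gives unadjusted false-positive rates of about 13% to 22% in the roughly 11% of trials with a chance entry difference of at least 0.5 SD; averaged over all trials the rate stays at about 5%. At a correlation of 0.3 the gain is only about 3%. These figures assume equal arms of 20 and a normal outcome. Priority is low, because the comparison is a preliminary secondary one in a pilot and the primary outcome of completing the 5 weeks is unaffected.

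**What to change.** In Outcome measures, state that the same record items will be extracted for a fixed window before randomisation, for example the 30 days that Background refers to, and reported by arm. If the entry form already holds drug use, say so and use it.

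In Planned analysis, compare use during the trial adjusted for the pre-randomisation value: ANCOVA for amounts, and a comparison stratified by entry use (yes/no) for binary use. Any table of cessation by entry use within condition should be labelled descriptive, since at an assumed 50% prevalence each cell holds about 20 × 0.5 = 10 participants.

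The cost is a slightly longer look-back in records already accessed, the additional entry values, and possibly a minor amendment or consent wording for the earlier dates. It needs no extra visit or procedure.
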